##### Safety

The safety of the intervention will be monitored via daily logs (record of adverse events) and will be ascertained by the qualified exercise professional and reviewed by the principal investigator during weekly meetings.

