#### Intervention Group

##### Overview

Our exercise program was informed by expert guidelines on exercise prescription in solid organ transplant recipients [12,20,41] and will be delivered by an exercise professional with experience in chronic disease management. Following the baseline assessment and randomization, intervention participants will receive an individualized, home-based exercise program consisting of aerobic and resistance training exercises for 12 weeks. The exercise prescription targets the Canadian Physical Activity guidelines [42], which recommends ≥150 minutes of at least moderate-intensity aerobic training per week and at least two days per week of resistance training for major muscle groups. Daily exercise practice will be unsupervised; however, the exercise professional will provide the exercise prescription during the first training session via videoconference, including the following: an assessment of the participant’s ability to exercise independently in their home environment (eg, review of the participants’ heart rate, blood pressure, and history of any pertinent injuries), demonstration and review of training techniques, and proper use of their Fitbit and exercise equipment.

Participants will also receive a detailed manual describing the importance of exercise and self-management skills for exercise behaviors based on the theory of planned behavior and social cognitive theory adapted from previous studies [43,44]. The manual will highlight the basics of exercise training, the importance of routines, principles related to exercise progression, and photographs with descriptions of the prescribed exercises. After the initial training session, the exercise professional will follow up weekly (via videoconference) with study participants to address potential barriers to exercise, provide motivational support, review symptoms or adverse events during independent training at home, and prescribe training progression. The exercise program will be tailored to the specific and changing needs of the participant, taking into consideration comorbidities, exercise capacity, physical function, and availability of training equipment. Details on exercise prescription for the intervention group are briefly provided and described in Table 3.

**Table 3 table3:** Exercise prescription details for participants in the intervention group.

Modality and frequency	Intensity	Time and volume of exercise	Type of exercise	Progression

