##### Safety Precautions for Remote Exercise Training

Participants will be instructed to discontinue exercise training if they experience any symptoms or feel unwell and will be strongly encouraged to immediately contact a member of the research team upon noticing any adverse events. Participants will be advised to reduce the intensity of their training if they reach ≥15 on the Borg RPE scale, if oxygen saturation is less than 85%, or if they experience any symptoms (eg, severe shortness of breath). If participants report chest pain or discomfort (ie, uncomfortable feeling of pressure, pain, squeezing, or heaviness in the chest spreading to the shoulder, arms, neck, and back), they will be instructed to stop and rest and seek emergency assistance if the discomfort persists for 5 minutes.

Participants who communicate medically concerning adverse events (eg, cardiovascular event or disease exacerbation) or contraindications to the exercise program will have their training suspended until clearance is provided by the study physician and the exercise professional. If participants sustain an injury because of participating in the study, the study team will ensure that appropriate medical treatment is received.

Before initiating any interaction with study participants, the study team will perform an objective assessment (ie, by measuring oxygen saturation, blood pressure, and heart rate if participants have a pulse oximeter or a blood pressure monitor at home). A subjective assessment of the study participants (eg, self-reported breathlessness, dizziness, and chest pain) will ascertain their suitability to proceed with testing, training, and progress with the exercise prescription. The study team will discuss with participants aspects of their home environment, availability and suitability of exercise training equipment, home walking space, and any potential safety concerns (eg, footwear, rugs, clutter, and pets). During the internet-based training sessions, participants will be supervised by the study team via a videoconference platform. Participants will be able to book additional sessions with the exercise professional if any concerns or questions arise.

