#### Primary Outcomes

##### Feasibility

The feasibility of a larger RCT to assess intervention efficacy (ie, phase 3 clinical trial) will be assessed through recruitment rates, program adherence, contamination, attrition, and safety at the end of the 12 weeks.

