#### Secondary Outcomes

Preliminary efficacy data will be collected at baseline and 12-week assessments (or the last recorded day of program completion). Details on the study measures by time point are presented in Table 2.

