##### Clinical Parameters

A liver transient elastography (FibroScan) assessment will be performed in liver transplant recipients to assess the degree of liver fibrosis (thickening and scarring of tissues) and steatosis (the amount of fat in liver tissue). Medical charts will be reviewed to collect data on age, sex, transplant type, the model for end-stage liver disease and lung allocation score, and detailed medication history through pharmacy records with cumulative and average daily doses of prednisone (mg/day) and calcineurin inhibitors, mTOR inhibitors, and antimetabolites (mycophenolate mofetil). Furthermore, liver enzymes along with total bilirubin, hemoglobin, and renal function (creatinine) levels will be abstracted from chart review. Data on posttransplant hospital admissions, allograft rejection, and cardiovascular comorbidities will also be ascertained from medical charts from the time of transplant to the end of the study period. Lifestyle factors, such as current alcohol consumption and smoking, will be ascertained from the chart review.

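### The safety outcome is built on participant self-report and is not linked to the chart-abstracted events the trial already collects, so serious or delayed events may be left out of the safety summary

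*Protocol article*

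**What the plan says.** The Feasibility section under Primary Outcomes states that the case for a phase 3 trial "will be assessed through recruitment rates, program adherence, contamination, attrition, and safety at the end of the 12 weeks". Safety is thus one of the results on which the pilot will be judged. Table 1, which lists the primary outcomes, has rows for recruitment, retention, adherence and satisfaction, and none for safety.

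The Safety section names the source: "The safety of the intervention will be monitored via daily logs (record of adverse events) and will be ascertained by the qualified exercise professional". The entries are then "reviewed by the principal investigator during weekly meetings".

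Two other reporting routes appear elsewhere. In the Intervention Group overview, the weekly videoconference is used, among other things, to "review symptoms or adverse events during independent training at home". In Safety Precautions for Remote Exercise Training, participants "will be strongly encouraged to immediately contact a member of the research team upon noticing any adverse events".

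Two further sources bear on safety without being named as part of it. The Retention section collects reasons for dropping out or interrupting training. Clinical Parameters, under Secondary Outcomes, states: "Data on posttransplant hospital admissions, allograft rejection, and cardiovascular comorbidities will also be ascertained from medical charts from the time of transplant", with a window that runs to the end of the study. Table 2 also lists hospital admissions, from charts, at baseline and 12 weeks.

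For controls, the Control Group section describes contact every 2 to 4 weeks about activity logs and trackers, without mentioning adverse events. Proposed Data Analyses summarizes safety in the intervention group.

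**The concern.** All three routes by which an event is described as reaching the study team (log entry, weekly call, unprompted contact) require the participant to report it. Someone who is admitted, injured or withdraws is plausibly the person least able or willing to fill in a daily log or join a call. Loss of safety information would then be related to the event itself, and the more serious the event, the greater the risk of losing it. The weekly call is also described around events during home training, which does not clearly cover an event that emerges hours or days after a session.

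The chart review does not depend on the participant in this way. It covers much of what one would most want to know, but it is filed under secondary clinical parameters. At stake is whether the safety summary used to support a phase 3 trial reflects what the trial dataset as a whole contains.

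**Working it through.** The article states no safety figure, event rate or capture rate, so there is nothing to reproduce. The main check is to set the sources side by side.

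| Source | Section | Depends on participant reporting? | Linked to the safety outcome? |
|---|---|---|---|
| Daily logs | Safety | Yes | Yes, the named source |
| Weekly call | Intervention Group, Overview | Yes | Not stated; described around training |
| Spontaneous contact | Safety Precautions | Yes | Not stated |
| Reasons for dropout or interruption | Retention | Largely | No |
| Charts: admissions, rejection, cardiovascular comorbidities | Clinical Parameters; Table 2 | No | No |

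The only source that does not rely on the participant is not connected to the outcome.

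The following is for scale only; event risks and capture shares are assumptions.

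*Inputs.* The Sample Size section gives 10 per study group and transplant type, so the intervention arm has 10 × 2 = 20. The Retention criterion is 80% or more, so it can be met with up to 0.20 × 20 = 4 of them lost. That is a threshold, not an expected loss.

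*Chance of recording at least one event.* With true risk p per participant and share c of events captured, this is 1 − (1 − p·c)^20.

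| p | c = 100% | c = 80% | c = 50% |
|---|---|---|---|
| 5% | 1 − 0.95^20 = 64% | 1 − 0.96^20 = 56% | 1 − 0.975^20 = 40% |
| 10% | 1 − 0.90^20 = 88% | 1 − 0.92^20 = 81% | 1 − 0.95^20 = 64% |
| 20% | 1 − 0.80^20 = 99% | 1 − 0.84^20 = 97% | 1 − 0.90^20 = 88% |

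Half capture at a true risk of 10% gives the same chance of seeing an event as full capture at 5%.

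*What zero recorded events would exclude.* The exact one-sided 95% upper limit is 1 − 0.05^(1/n). For n = 20 it is 13.9%. If 4 participants supply no safety data, n = 16 and it is 17.1%. The second figure is valid only if those 4 are missing for reasons unrelated to events. If they left because of an event, no such limit applies.

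**The case against.** The strongest reply is that the plan is not log-only. Spontaneous reporting covers any adverse event, with no restriction to training. The logs are daily and are not expressly limited to exercise days. The weekly call does not depend on logging. The exercise professional and the principal investigator both look at the entries. Reasons for dropout and interruption are collected, which is where an event that ends participation could surface. The description of the weekly call is a summary, not a script. Event definitions, grading and procedures may sit in a fuller document, and the article says standard operating procedures exist for all protocol elements.

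Much of this stands, and it rules out two stronger readings:

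- A reader might infer that serious events are missed by the trial. The documents do not support that. Admissions, rejection and cardiovascular comorbidities would be in the dataset through chart review. They would be absent from the safety outcome as defined, not lost.
- A reader might infer that safety follow-up ends when a participant stops the program, because the Secondary Outcomes section allows assessment at 12 weeks "or the last recorded day of program completion". That wording governs preliminary efficacy data. The Feasibility section places the assessment of safety at the end of the 12 weeks.

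What the reply does not remove is that every reporting route feeding safety still runs through the participant, and that no section ties dropout reasons or chart events to the outcome. This is not merely detail left to a fuller document: the article itself states the source of the safety data and itself places the chart events elsewhere. The missing Table 1 row is an inconsistency within the article.

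**Conclusion.** The concern holds in a limited form. A primary feasibility outcome is defined on participant-reported logs, while a more independent source that the trial already collects is left unlinked. Serious or delayed events, and events in people who stop logging or attending calls, may therefore be left out of the safety summary.

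The size of any under-count cannot be stated. The tabulated probabilities show only that, with 20 intervention participants, incomplete capture could matter. They rest on assumed risks of 5% to 20% and assumed capture of 50% to 100%. That under-reporting is related to the event is plausible but not shown by the documents.

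A related limit is that no comparable adverse event questioning is described for controls. Of the sources described, chart data therefore offer the most even basis for setting the arms side by side. The change is worth making because it is cheap and uses data already planned; it is not a flaw that invalidates the pilot.

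**What to change.** In the Safety section, define the outcome as all adverse events from randomization to week 12, whether or not the participant is still exercising or logging. Name the sources: daily logs, weekly calls (asking about any event since the last contact), spontaneous reports, recorded reasons for dropout or interruption, and the chart data described under Clinical Parameters. Because the chart window opens at transplantation, chart events need dates so that those after randomization can be separated.

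Report the chart-based events in both arms. Keep events found through the intervention arm's weekly calls separate from that comparison, since controls are not described as being asked in the same way.

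Add a safety row to Table 1 so that it agrees with the Feasibility section.

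The cost is protocol wording, a broader weekly question if the current one is as narrow as described, and linking data already collected. The downside is that more events unrelated to exercise will be recorded.

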##### Satisfaction

Satisfaction with the exercise program and other study interventions (eg, nutritional counseling) will be assessed at weeks 2 and 6 and at the end of the 12-week intervention via a satisfaction survey (multiple-choice questions) created by the research team. The control group will also complete a satisfaction survey in which participants will provide feedback on their experiences at the end of the study.

#### Secondary Outcomes

Preliminary efficacy data will be collected at baseline and 12-week assessments (or the last recorded day of program completion). Details on the study measures by time point are presented in Table 2.

##### Metabolic Risk Factors

Impaired glucose tolerance, abdominal obesity, cholesterol, and blood pressure will be assessed and classified according to the National Cholesterol Education Program Adult Treatment Panel III criteria [47]. More specifically, the following markers will be used to classify metabolic risks: (1) increased waist circumference (>102 cm [>40 in] for men, >88 cm [>35 in] for women); (2) elevated triglycerides of ≥1.7 mmol/L (≥150 mg/dL); (3) low levels of high-density lipoprotein: <1 mmol/L (40 mg/dL, male), <1.3 (50 mg/dL, female), or on cholesterol medication; (4) a resting blood pressure of ≥130/85 mm Hg or on hypertensive medication; and (5) fasting plasma glucose levels of 6.1 mmol/L (110 mg/dL) or on pharmacotherapy for diabetes. Participants will have the option of completing bloodwork either on-site or externally in a medical laboratory. Blood will be collected in a fasting state (no eating and drinking for 8 hours before testing; however, water is allowed) and includes a total cholesterol panel (ie, total cholesterol, triglycerides, low-density lipoprotein, and high-density lipoprotein), fasting blood glucose level, hemoglobin A_1c_ test, and C-reactive protein levels. Insulin resistance will be captured using the homeostatic model assessment for insulin resistance protocol (fasting insulin multiplied by fasting blood glucose). Finally, C-peptide levels will be analyzed in participants receiving exogenous insulin therapy.

##### Clinical Parameters

A liver transient elastography (FibroScan) assessment will be performed in liver transplant recipients to assess the degree of liver fibrosis (thickening and scarring of tissues) and steatosis (the amount of fat in liver tissue). Medical charts will be reviewed to collect data on age, sex, transplant type, the model for end-stage liver disease and lung allocation score, and detailed medication history through pharmacy records with cumulative and average daily doses of prednisone (mg/day) and calcineurin inhibitors, mTOR inhibitors, and antimetabolites (mycophenolate mofetil). Furthermore, liver enzymes along with total bilirubin, hemoglobin, and renal function (creatinine) levels will be abstracted from chart review. Data on posttransplant hospital admissions, allograft rejection, and cardiovascular comorbidities will also be ascertained from medical charts from the time of transplant to the end of the study period. Lifestyle factors, such as current alcohol consumption and smoking, will be ascertained from the chart review.

##### Physical Activity and Exercise Behaviors

Previous physical activity and exercise training habits will be collected at baseline by self-report (after discussion with the research team) and by completion of the Physical Activity Scale for the Elderly questionnaire [48], a short survey created to assess physical activity levels in older adults commonly applied in solid organ transplant recipients [9].

##### Physical Function

The short performance physical battery [49] test is used to assess gait, balance, and lower extremity performance. Participants will be asked to stand in one position holding their balance, rise from a chair 5 times, and walk for 4 m while being timed at their usual pace. For remote assessments (via videoconference), the balance test may be excluded if participants report a history of balance impairments or falls.

##### Body Composition

Weight, BMI, and body fat percentage will be measured via bioelectrical impedance analysis (Tanita, DC-430U) for participants coming on-site for study assessments; otherwise, participants will be asked to measure their weight at home if they have a scale. Participants will be asked to measure and record their body weight once a week. Height data will be obtained from the medical charts. For participants coming on-site for study assessments, waist circumference will be measured by the research team according to the World Health Organization standardized protocol. For participants completing the assessment remotely, waist circumference will be self-assessed using a measuring tape via videoconference under the direct supervision of the research team.

##### Nutritional Outcomes

The dietary habits of our study participants will be assessed using the Rapid Eating Assessment for Patients [50] questionnaire and a 3-day food record.

##### Health-Related Quality of Life

The 36-Item Short-Form Survey [51] will be used to measure mental and physical domains of quality of life in our participants (scores range from 0 to 100, with higher scores representing higher HRQL). The Short-Form 36 has been routinely applied in both OLT [30] and LTx recipients [52].

##### Self-efficacy

The Exercise Self-efficacy Scale [53], a Likert scale with 4-point rating in which participants rate their confidence levels with regard to carrying out regular physical activities and exercise, will be implemented to measure self-efficacy toward exercise.

##### Barriers to and Facilitators of Exercise

Familiarity and comfort levels surrounding technology, barriers to exercise, and evaluation of previous experience with exercise, especially within the home environment, will be captured using a questionnaire developed by our research team.

### Statistical Procedures

#### Sample Size

The sample size of 40 (10 per study group and transplant type) is in keeping with the recommendations for a pilot study to assess feasibility [54]. A power calculation was not performed for the secondary outcomes, as the main purpose of this study is to determine feasibility and obtain point estimates for a larger RCT. The liver transplant and LTx program at the University Health Network each has approximately 150 to 200 recipients per year. Furthermore, the rates of PTMS among LTx and OLT recipients range from 30% to 50%; thus, we anticipate an approximate eligible pool of 50 transplant recipients per year for each organ group. Our previous consent rates for rehabilitation studies in these populations have been approximately 30% to 50% [55,56].

#### Proposed Data Analyses

Descriptive statistics (means, SDs, or medians and IQRs) will be used for continuous variables, and frequencies will be used for categorical variables to summarize program adherence, participant satisfaction, contamination, attrition, and safety in the intervention group, and to compare any differences between LTx and OLT recipients across these parameters using 2-tailed *t* tests and tests of proportion. Estimates at baseline and 12 weeks within- and between-group will be reported using means and 95% CIs to derive effect estimates for sample size calculations in subsequent trials. Statistical analysis will be performed by a statistician who will be blinded to the group assignments. All eligible participants (N=40) will be included in the data analyses based on intention-to-treat, depending on the group to which they are randomized.

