##### Retention

Retention for the whole study and per group will be determined by the number of participants completing the final study assessment compared with the number of randomized participants. A retention rate of 80% or greater has been established as our criteria to determine study feasibility for future projects. The reasons for dropping out or interruptions to training will be collected.

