#### Data Management and Quality Assurance

Our research team is trained in the study requirements, measurement protocols, and has expertise in conducting physical assessments in solid organ transplant recipients. The research team has critically appraised the external peer-review comments from the Canadian Donation Transplant Research Program (Multimedia Appendix 1) and has incorporated them into the study protocol. Standard operating procedures have been generated for all the protocol elements. The accuracy of the data entered in our research database will be periodically audited by the research coordinator. The research team will attempt to have participants complete the entirety of the study assessments, and if there are incomplete data for a specific participant or missing responses to questionnaires, missing data will not be imputed. Participants will be closely monitored by the research team and the exercise professional to maximize study retention and assess exercise adherence rates during the 12-week intervention. Participants in the intervention group will be educated on the importance of adhering to the intervention, logging progress, and completing study assessments. The research team will send reminders to intervention participants for weekly meetings, and study assessments will be booked at convenient times for participants.

The study participants will have a random identifier generated with only the coded identifier attached to the participant data. The study data will be stored on a password-protected server following the currently established institutional and national research ethics and privacy guidelines. The study information will be accessible only to approved study members. In the event of an inappropriate release of personal health information to an unauthorized party, we will take the appropriate steps to minimize any potential harm: (1) further release of information will be stopped, (2) an attempt to retrieve all inappropriately released information will be made, and (3) the sponsor’s privacy office and research ethics board will be immediately notified.

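### All 40 are promised in an intention-to-treat analysis, but missing 12-week values are not imputed and the final measurement may fall on an earlier program day, so who and what the 12-week means describe is left open

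*Protocol article*

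**What the plan says.** Four statements in the protocol article bear on who enters the 12-week comparison and when they are measured.

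- **Analysis population** (Proposed Data Analyses): "All eligible participants (N=40) will be included in the data analyses based on intention-to-treat", by the group to which they were randomised.
- **Estimates** (same section): "Estimates at baseline and 12 weeks within- and between-group will be reported using means and 95% CIs". They are intended for sizing later trials.
- **Missing data** (Data Management and Quality Assurance): after an attempt to complete all assessments, "missing data will not be imputed".
- **Timing of the final measurement** (Secondary Outcomes): "Preliminary efficacy data will be collected at baseline and 12-week assessments (or the last recorded day of program completion"; the parenthesis closes there, with no further definition.

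Retention, a primary feasibility outcome, is defined in the Retention section as "the number of participants completing the final study assessment compared with the number of randomized participants". The same section sets the criterion: "A retention rate of 80% or greater has been established as our criteria to determine study feasibility for future projects".

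**The concern.** Inclusion of all 40, 12-week means and no imputation are compatible only if all 40 have a 12-week value. The plan itself expects that some may not, since it calls 80% retention acceptable. The article does not say what then happens, and the Secondary Outcomes alternative makes the answer less clear. A participant who stops early is either left out of the 12-week mean or represented by a measurement taken after a shorter exposure. These are different estimates, and the text does not choose between them.

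Two uses of the results are affected. The between-group estimates are to feed later sample size calculations, so it matters whether they describe everyone randomised at week 12, those who completed, or a mixture of exposure times. Retention also has a threshold attached, so what counts as the final assessment must be unambiguous.

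There are reasons to think that loss could differ between the arms. Only the intervention arm follows a 12-week exercise program, and its participants can have training suspended for medical reasons. Contact also differs: weekly videoconferences and reminders in the intervention arm, against correspondence every 2 to 4 weeks in the control arm.

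**Working it through.** **Inputs from the article.** Sample size is 40, from 10 per study group and transplant type (Sample Size). Allocation is 1:1 (Randomization). The retention criterion is 80% (Retention). No SD, effect size or dropout pattern is given, so results below are in SD units.

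**Step 1: the plan's own figure.** 10 × 2 groups × 2 transplant types = 40, or 20 per arm. This reproduces.

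**Step 2: number with a final assessment at the threshold.** 0.80 × 40 = 32, so 8 may lack one.

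**Step 3: how likely is a complete 40?** If each participant completes independently with probability r (an assumption), the chance that all 40 do is r^40.

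| r | r^40 |
|---|---|
| 0.95 | 0.129 |
| 0.90 | 0.015 |
| 0.80 | 0.00013 |

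Some missing 12-week values should therefore be expected.

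**Step 4: precision of a simple comparison of means.** The half-width of the 95% CI in SD units is t(0.975, n1 + n2 − 2) × √(1/n1 + 1/n2).

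| Analysed | Calculation | Half-width | Ratio to 20 v 20 |
|---|---|---|---|
| 20 v 20 | 2.024 × 0.3162 | 0.64 SD | 1.00 |
| 16 v 16 | 2.042 × 0.3536 | 0.72 SD | 1.13 |
| 12 v 20 | 2.042 × 0.3651 | 0.75 SD | 1.16 |

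**Step 5: possible bias if early stoppers are left out.** With loss in one arm only, bias = (fraction lost in that arm) × (gap between completers and dropouts). The gaps are assumptions; the article gives none.

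| Assumed gap | 4 of 20 lost | 8 of 20 lost |
|---|---|---|
| 0.25 SD | 0.05 SD | 0.10 SD |
| 0.5 SD | 0.10 SD | 0.20 SD |
| 1.0 SD | 0.20 SD | 0.40 SD |

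If the fraction lost and the gap are the same in both arms, the bias is 0.

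**Step 6: the alternative reading.** If a value from the last program day is used, the participant is observed and can be among the 40. With 4 of 20 such participants in the exercise arm, that arm's mean is (16/20) × the week-12 mean + (4/20) × the mean at assorted earlier dates. The control arm has no exercise program, so the article supplies no evident equivalent date for a control participant who leaves. Steps 4 and 5 do not apply to a participant handled this way: the two consequences are alternatives for any one person.

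**Step 7: retention.** Each early visit counted as a final assessment adds 1/40 = 2.5 percentage points. With 31 week-12 assessments retention is 31/40 = 77.5%, below the criterion; one early visit counted makes it 32/40 = 80%, which meets it.

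**The case against.** The strongest defence is that nothing here defeats intention-to-treat. The article ties that term to the assigned group, and declining to impute does not prevent analysis as randomised. A likelihood-based model using all observed values would comply with the no-imputation rule, and an analysis plan that is not shown may name one. A reader might infer that the promised analysis cannot be delivered at all. The documents do not support that: it can be delivered with full follow-up, and the difficulty arises only once a 12-week value is missing. What survives is narrower. The article commits to 12-week means on all 40 while accepting that up to 8 may have no final assessment.

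Second, Secondary Outcomes says when data are collected. It does not mention dropouts or say that an early value is analysed as week 12, and Table 2 lists only baseline and 12 weeks for these measures (plus weeks 2 and 6 for exercise self-efficacy). A reader might infer that a dropout's last program day stands in for week 12. That is a natural reading, but it is not stated. The valid criticism is that the phrase permits it and leaves it undefined.

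Third, the retention risk is conditional. Table 1 measures retention by attrition, and reasons for dropping out are recorded separately. Nothing says that a dropout counts as retained; the text only fails to exclude it.

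Fourth, the wider interval is the cost of losing 8 people under any plan. A mixed model would not restore 0.64 SD, because participants with baseline only add almost nothing on the 12-week difference. Nor would it by itself correct informative dropout.

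Finally, the team does undertake to attempt complete assessments, and remote visits are available. That helps, but it does not say that people who stop the program are still assessed at week 12.

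**Conclusion.** The point holds as an unresolved conflict between stated rules. Once any 12-week value is missing, following the text gives one of two results: a 12-week mean on fewer than 40 people, or an estimate on more people that mixes exposure times under a rule with no clear control-arm counterpart. At the plan's own threshold the first result means 32 analysed and a half-width of about 0.72 SD instead of 0.64 SD, assuming an even split and a simple comparison of means.

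The size and direction of any bias are unknown. A reader might take the 0.10 SD entry in the bias table and conclude that a true 0.40 SD would be reported as 0.50 SD, 25% too high. That needs a 0.5 SD gap and loss of 4 of 20 in the exercise arm only, neither of which is in the documents.

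Severity is should-fix. Efficacy is secondary in this pilot and no power calculation depends on it. However, the estimates are meant to size later trials, and retention is a primary criterion whose numerator should not depend on an undefined visit.

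**What to change.** 1. In Secondary Outcomes, delete the parenthesis that offers the last program day. State that the final assessment is sought at 12 weeks from randomisation in everyone randomised, in both arms, whether or not they continue the program. The remote visits already described under Study Assessments can be used. This is the change that addresses informative dropout, because it reduces the missing data.
2. In Retention, count as retained only those with an assessment inside a stated week-12 window, the same for both arms.
3. In Proposed Data Analyses, replace the sentence beginning "All eligible participants (N=40) will be included in the data analyses based on intention-to-treat" with analysis of all randomised participants in their assigned group using all observed outcomes, and report the number analysed per arm for each outcome. Using randomised in place of eligible also avoids confusion with the Recruitment section, where eligible describes the larger pool approached.

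A likelihood-based model is optional. It is compatible with the no-imputation rule, but it is no substitute for the first change.

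The cost is protocol wording, a few extra remote visits to people who have stopped the program, and possibly a slightly lower retention figure.
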